**Figure 2 F2:**
[figure not shown]
ENGAGED Intervention Timeline.

### Standard weight loss program (STND)

STND participants will be given a goal of 7% weight loss to be achieved through changes in diet and activity, similar to the DPP lifestyle intervention
[32]. Based on baseline weight, participants will be given daily calorie goal between 1200–2000 kcal/day and a 25% fat gram goal between 32–55 grams/day. These goals are designed to produce a one to two pound weight loss per week. Participants will also be given a weekly physical activity goal, beginning with 45 minutes of moderate intensity physical activity per week and progressing weekly to 175 minutes per week. Participants will be provided with “The Complete Book of Food Counts”
[33] and paper Keeping Track diaries during months 1–6 to facilitate self-monitoring of dietary intake, physical activity, and body weight.

The original sixteen session DPP protocol will be condensed to eight group sessions (see Table
2) and, similar to the Look AHEAD trial
[34], group sessions will be combined with individual telephone coaching to increase social support and reduce costs
[35]. Group sessions will run 90 minutes in duration and be held weekly for the first eight weeks of the study. Each group session will begin with a private weigh-in and participants will submit their Keeping Track diary. All group sessions will be led by a trained lifestyle interventionist and will include setting an agenda, reviewing homework and self-monitoring, presentation of new material, group discussions, and assignment of homework. See Table
2 for a list of session topics. All group sessions will end with an optional supervised group walking session.

**Table 2 T2:** ENGAGED Study Group Session Topics

**Session**	**Topics covered**
1	Getting Started With Activity and Healthy Eating
	Be a Fat Detective
2	Three Ways to Eat Less Fat
	Four Keys to Healthy Eating Out
3	Take Charge of What’s Around You: Making Cues Work for You
4	Move Those Muscles and Be Active As A Way of Life!
5	You Can Manage Stress
	Talk Back to Negative Thoughts
6	Tip the Calorie Balance
	Problem Solving
7	Healthy Eating
	The Slippery Slope of Lifestyle Change
8	Jump Start Your Activity Plan
	Ways to Stay Motivated

In addition to in-person group sessions, STND participants will receive individual coaching calls. Coaching calls will be scheduled on a weekly basis during the initial eight weeks of the study and monthly during months 3–6. Coaches will review submitted Keeping Track diaries and determine the participant’s level of achievement for each goal using standardized adherence criteria for the study. Coaching calls will last approximately 10–15 minutes and follow a structured script aiming to reinforce success and problem solve around barriers to change. Four content areas will be covered during each call: (1) weight loss, (2) adherence to dietary and physical activity self-monitoring, (3) attainment of diet and activity goals, and (4) goal setting.

### Technology-supported weight loss program (TECH)

Similar to STND, TECH will attend eight in-person group sessions, receive regular coaching calls, and follow the same weight, physical activity, and dietary goals. However rather than paper Keeping Track diaries, TECH will be provided with a study smartphone, ENGAGED application, and an accelerometer to use during the first 6 months of the intervention. In addition to covering the topics discussed during the first group meeting (Table
2), TECH will be instructed on how to self-monitor dietary intake, use the accelerometer, and communicate virtually with their teammates and coach using the ENGAGED application. Time-stamped dietary and physical activity data will be continuously downloaded to a secure server, and participant data will be summarized automatically on the secure coaching application and website, allowing coaches to have up-to-date access to participant data, enabling corrective or supportive feedback to be given via text message or during scheduled coaching calls.

### ENGAGED technology

The ENGAGED technology includes a study smartphone (Motorola Droid™), pre-loaded with the ENGAGED application, and an accelerometer (SHIMMER™). TECH participants will use the ENGAGED application, which contains the CalorieKing® food database, a comprehensive nutritional source containing over 50,000 food entries, to self-monitor daily dietary intake. Goal thermometers will display participant’s goal and actual amount of calories and fat grams consumed (Figure
3). The ENGAGED application also includes a Team tab that allows participants to view team members’ adherence to self-monitoring and accelerometer usage. In addition, the Team tab on the application includes a message board and peer-to-peer messaging to facilitate communication and support among teammates. Participants will also wear an accelerometer that connects via Bluetooth to the smartphone to provide real-time objective data on the accumulation of moderate-to-vigorous intensity physical activity. In the event participants engage in an activity not captured by the accelerometer (i.e. cycling, swimming), users may manually input physical activity.

**Figure 3 F3:**
[figure not shown]
Screen shot of ENGAGED smartphone application.

### Self-guided behavioral weight loss program (SELF)

SELF will attend one 60-minute in-person group session during but will not attend any additional group sessions nor receive coaching calls throughout the intervention. Similar to STND, SELF will be given “The Complete Book of Food Counts”
[33] and paper Keeping Track diaries. Rather than attend in-person group sessions, SELF will receive three Group Lifestyle Balance™ (GLB) Program DVDs
[36] that contain 12 group sessions adapted from the original DPP curriculum as well as the corresponding GLB participant handouts. SELF will be given their individual 7% weight loss goals and instructed to watch the DVDs to get their calorie and fat gram goals.

### Team weight loss competition

In order to encourage members of each weight loss team to support each other’s behavioral adherence and weight loss, a team weight loss competition will be held at 3- and 6-months during each cohort. The team with the greatest weight loss percentage at each time point will win $400, to be divided evenly among the group members ($50 per team member).

### Treatment fidelity

Fidelity checklists will be prepared for group and telephone coaching sessions. Checklists for each session will specify a) good counseling practices; b) prescribed session content; and c) proscribed session content. Coaches will undergo training to become familiarized with the modified DPP protocol and to role-play potential conflicts and situations that may arise during group and telephone sessions. Study staff will also attend weekly clinical meetings to discuss any participant conflicts that may arise. All group and telephone coaching sessions will be audio recorded, and each month a random sample of 10% of the recordings will be coded by study staff to evaluate treatment fidelity. If fidelity falls below 90% on any of the fidelity checks, staff will be retrained.

### Outcome measures

Assessments will be completed at baseline, 3-, 6-, and 12-months. Participants will receive $40 for completing each of the 3-, 6, and 12-month assessments. The procedures and measures are described below:

#### Height, weight, BMI, and waist circumference

Height will be measured using a wall-mounted stadiometer to the nearest 0.01 cm. Body weight will be measured without shoes, wearing light clothing on a calibrated beam balance scale to the nearest 0.01 kg. BMI (kg/m^2^) will be calculated using height and weight measurements. Waist circumference will be assessed by positioning an anthropometric tape midway between the palpated iliac crest and the palpated lowest rib margin in the mid-axillary lines. Two measurements will be taken and the mean value of each site will be used.

#### Dietary intake adherence

Dietary intake will be assessed at baseline, 3-, and 6-months via interview by a non-intervention registered dietician using the computer-assisted telephone interview (CATI) 24 hour recalls
[37] using the multiple pass method to assess calorie and fat intakes. At each time point, three days (one weekend and two weekdays) will be randomly selected over a three week period to conduct the recalls. The data derived from the recalls will be analyzed using the annually updated University of Minnesota Nutrition Coordinating Center’s (NCC) Nutrition Data System for Research (NDS-R-2005). Only STND and TECH will complete dietary recalls at 3- and 6-months.

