### Study aims

Guided by CST and social networks research, the ENGAGED study will evaluate the feasibility and efficacy of a technology-supported weight loss program for obese adults. Specifically, the primary aim of the ENGAGED study is to conduct a three-group randomized controlled trial testing the efficacy of the ENGAGED technology-supported behavioral weight loss program, as compared to the same program delivered using standard paper and pencil self-monitoring, and self-guided behavioral weight loss supported by participants receiving DVD’s depicting DPP treatment. Primary outcomes include: (1) weight loss and (2) behavioral adherence, which is operationalized by (a) self-monitoring of diet and activity and (b) attainment of diet and activity goals. As a secondary outcome, the time spent administering the intervention by lifestyle coaches will also be examined to assess intervention costs. The second aim of the ENGAGED study is to test whether the weight loss in the technology-supported condition is mediated by behavioral adherence to self-monitoring and achievement of diet and activity goals.

We hypothesize that using a theory-guided, technology-supported weight loss treatment will result in clinically significant weight loss with fewer in-person sessions by preserving regular social support, accountability, and feedback via mobile technology. Further, we hypothesize that technology-supported weight loss treatment will result in greater weight loss compared to the traditional paper self-monitoring approach.

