### Data analytic plan

#### Linear mixed modeling

Data will be analyzed on an intent-to-treat basis. The basic modeling approach will entail linear mixed models for longitudinal data. The primary aim is to test for treatment group differences on weight loss at 3-, 6-, and 12-months as well as differences in behavioral adherence and goal attainment at 3- and 6-months. Linear mixed models do not require that participants are measured at all time points, and therefore can include participants with missing data across time. In these analyses, we will examine changes across time by treating time as a nominal variable in the analysis to allow for non-linear trends. In addition to the effect of time, the main independent variable is treatment groups, a between-subjects factor with 3 levels: STND, TECH and SELF. A priori Helmert contrasts
[38] will be used to test the following comparisons at 3- and 6-months: 1) STND and TECH vs. SELF and 2) TECH vs. STND. We will also examine group by time interactions to test whether change in outcome across time differs by group.

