### Sample size and power

We will randomize n=32 participants to each treatment group and assume 6% of participants will drop out by the end of the study so that there will be n=30 participants in each group at the final endpoint. The power calculations below are based on the second Helmert contrast: TECH vs. STND because this contrast contains the fewest number of subjects (30 in each group) and we expect this contrast to have the smallest effect sizes. The first Helmert contrast: STND and TECH vs. SELF has a larger sample size (60 vs. 30) and we anticipate larger effects sizes in this contrast due to the limited intensity of the SELF intervention. Therefore, by powering the study based on the second contrast, we will have more than adequate power for the first contrast.

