#### Dietary intake adherence

We measure adherence to calorie goals at 3 and 6 months using 3 day 24 hour recalls. Using pilot data from a previous trial, we observed a standard deviation of change in calories of 498 at month 3 and 431 at month 6, with a correlation of 0.9 between the two time points. With 80% power and an n=30 in both groups, we will be able to detect a calorie reduction difference of 375 calories.

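### SELF has no dietary recalls at 3 or 6 months, so the STND and TECH vs. SELF contrast cannot be estimated for diet goal attainment and its power claim cannot hold for that primary outcome

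*Protocol article*

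**What the plan says.** All references are to the protocol article.

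- **Study aims** lists two primary outcomes for the three-group comparison. The second, behavioral adherence, includes component "b) attainment of diet and activity goals".
- **Sample size and power, Dietary intake adherence** names the instrument: "We measure adherence to calorie goals at 3 and 6 months using 3 day 24 hour recalls".
- **Outcome measures, Dietary intake adherence** sets recalls at baseline, 3 and 6 months, then limits the follow-up recalls: "Only STND and TECH will complete dietary recalls at 3- and 6-months".
- **Linear mixed modeling** includes in the primary aim "differences in behavioral adherence and goal attainment at 3- and 6-months". Treatment group is "a between-subjects factor with 3 levels: STND, TECH and SELF". The Helmert contrasts "will be used to test the following comparisons at 3- and 6-months: 1) STND and TECH vs. SELF and 2) TECH vs. STND".
- **Sample size and power** gives the first contrast 60 vs. 30 participants and concludes that "by powering the study based on the second contrast, we will have more than adequate power for the first contrast". The calorie calculation is one of those that this paragraph introduces.

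**The concern.** These statements cannot all hold. A primary outcome is to be compared between SELF and the other two arms at visits where SELF is not measured. This is not missing detail that a fuller document might supply. One section sets the data collection and two others state an analysis and a power claim that it rules out.

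Three consequences follow.

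- An analyst who follows the plan literally gets no estimate of the first contrast for diet.
- If the group-by-time interaction were dropped, software would still print a first contrast. It would rest only on SELF's baseline recalls and say nothing about the intervention.
- Diet goal attainment could not serve as a mediator in a three-arm model. A mixed model tolerates missing outcomes, but not a covariate missing for a whole arm, so SELF would drop out.

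**Working it through.** **1. The plan's own figure (second contrast, TECH vs. STND).** Inputs from Sample size and power: 30 per group, 80% power, SD of calorie change 498 at month 3 and 431 at month 6, correlation 0.9, stated detectable difference 375 calories. The type I error is not stated; 0.05 two-sided is assumed.

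MDD = (z₀.₉₇₅ + z₀.₈₀) × SD × √(1/n₁ + 1/n₂)

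- Month 3 SD: 2.80 × 498 × √(2/30) = 360 (366 with the t distribution). Power at 375 is 0.83 (0.82 with t).
- Mean of the two months: SD = √[(498² + 431² + 2 × 0.9 × 498 × 431)/4] = 453, MDD = 328, power at 375 = 0.89.

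The 375 is reproduced closely with the month 3 SD and is conservative under the averaged SD. It is not in dispute.

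**2. Participants with a recall outcome, at the plan's 30 per arm after dropout (32 × 0.94 ≈ 30).**

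| Arm | Month 3 | Month 6 |
|---|---|---|
| STND | 30 | 30 |
| TECH | 30 | 30 |
| SELF | 0 | 0 |

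**3. Estimability.** The plan specifies "treating time as a nominal variable in the analysis to allow for non-linear trends" and group-by-time interactions. Over baseline, month 3 and month 6 the model has 3 × 3 = 9 cell means. SELF at months 3 and 6 is empty, so the design matrix has rank 7 of 9.

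As change from baseline at visit t, the contrasts are:

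- First: ½(STNDₜ − STND₀) + ½(TECHₜ − TECH₀) − (SELFₜ − SELF₀). This needs SELF₃ or SELF₆, for which there are no data. Adding the contrast row raises the rank, so it is not estimable at month 3 or month 6.
- Second: (TECHₜ − TECH₀) − (STNDₜ − STND₀). All four cells are observed, so it is estimable at both visits.

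The variance of the first contrast at a single visit shows the same thing: σ²[1/(4·n_STND) + 1/(4·n_TECH) + 1/n_SELF] has no finite value when n_SELF = 0. Nominal time leaves no trend by which to carry SELF forward from baseline.

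**4. What the power claim presupposes.** Had SELF been recalled, 60 vs. 30 would give:

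| SD used | MDD, 80% power | Power at 375 calories |
|---|---|---|
| 498 (month 3) | 312 | 92% |
| 431 (month 6) | 270 | 97% |
| 453 (mean of both) | 284 | 96% |

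The claim would then be sound. It fails for diet because the 30 SELF observations do not exist, not because of an arithmetic error.

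**5. Another source for SELF?** The article gives none. SELF keeps paper diaries, but Dietary self-monitoring adherence scores them only as days recorded. Coaches rate goal achievement from diaries as part of the coaching calls (Standard weight loss program), and SELF receives no calls (Self-guided behavioral weight loss program).

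**The case against.** The strongest reply is that the restriction is openly stated where the outcome is defined, so it looks deliberate. The only diet-specific power statement concerns two groups of 30, which fits TECH vs. STND. No hypothesis or detectable difference is given for SELF on dietary intake, and a reader might infer a two-arm analysis. That limits the harm, but the modeling section specifies three levels and both contrasts for the whole primary aim, and the outcome section draws no analytic consequence from the restriction.

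A second reply is that mixed models accommodate missing data, as the article says. That covers participants who miss visits. It does not identify a visit mean for an arm that is unobserved by design.

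Three narrower points stand as limits on the finding:

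- The power paragraph is a general argument and contains no miscalculated figure. Its failure for diet follows from the same mismatch and is not a second defect.
- The misleading-output scenario needs a model without the interaction, whereas the article says interactions will be examined. The likelier result is a contrast that visibly cannot be estimated.
- The mediation model names self-monitoring adherence, which SELF does have. The problem arises only if diet goal attainment, which the aims and the mediation hypothesis also name, is entered in a three-arm model. The TECH vs. STND effect can be examined without SELF.

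**Conclusion.** The concern holds. For recall-based diet goal attainment the first Helmert contrast has 60 vs. 0 participants at both 3 and 6 months. It cannot be estimated, and the claim of more than adequate power cannot be true of it. Estimability does not depend on any assumed SD or error rate. It rests on three stated features: no follow-up recalls in SELF, nominal time and visit-specific contrasts. It also rests on the article giving no other measure of diet goal attainment for SELF.

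The scope is one contrast on the dietary half of one component of the second primary outcome. The plan should be corrected because the comparison it promises is a primary one, but the weight comparison and the study's sample size are not affected.

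**What to change.** - **Outcome measures, Dietary intake adherence:** state that recall-based diet adherence is a two-arm outcome at 3 and 6 months.
- **Linear mixed modeling:** add that its model is fitted in TECH and STND only and that only the second contrast is tested.
- **Mediation analysis:** restrict any dietary goal-attainment mediator to TECH vs. STND.
- **Sample size and power:** exclude dietary intake from the statement about the first contrast.
- **Reporting:** limit conclusions about SELF to weight, self-monitoring and accelerometer activity.

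This costs wording only. No new recalls are needed, and the comparison given up was never obtainable. Keeping that comparison would instead require follow-up recalls in SELF: 32 participants × 2 visits × 3 days = 192 interviews, and only if those visits still lie ahead.

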#### Physical activity adherence

Physical activity will be objectively measured by an accelerometer (Actigraph #7164, Pensacola, FL) over 7 days at baseline, 3-, and 6-months. The accelerometer will be attached to an elastic belt and worn on the right hip. Minutes of moderate-to-vigorous intensity physical activity will be measured in a modified bout lasting a minimum of eight consecutive minutes. Adherence will be ascertained on the basis of how well the participant’s bout-corrected accelerometer count corresponds to the weekly activity goal.

#### Dietary self-monitoring adherence

Dietary self-monitoring adherence will be assessed as the number of days reporting dietary intake on the paper Keeping Track diaries (STND and SELF) or smartphone application (TECH). In order to receive full adherence credit for a day of self-monitoring, participants must have ≥ 1000 calories recorded and ≥ 25 grams of fat.

#### Physical activity self-monitoring adherence

For STND and SELF, physical activity self-monitoring adherence will be assessed as the number of days reporting physical activity in the paper Keeping Track diaries, divided by the number of possible days. For TECH participants, self-monitoring adherence will be operationalized as the number of days the accelerometer was worn ≥ 8 hours, divided by the number of possible days.

#### Coaching time

Coaches will monitor the number of minutes preparing for and conducting individual coaching calls throughout the first 6 months of the intervention.

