## Discussion

Obesity continues to be a significant public health issue worldwide and guidelines recommend intensive behavioral interventions for all obese adults
[1,2,40]. However, efficacious and scalable interventions have not yet been widely implemented. Mobile technology provides an opportunity to develop interventions with lower costs, less burden, and a greater reach, particularly as mobile usage rates continue to rise. As of February 2012, approximately 46% of American adults currently own a smartphone, an increase from 36% in May 2011
[26]. Minority groups, including Blacks and Hispanics saw an increase in smartphone use from 44% to 49% during this same time period
[26]. Smartphones have the ability to extend key components of intensive weight loss treatment into real-world settings, while reducing treatment costs and maintaining efficacious weight loss outcomes. The ENGAGED study is an innovative randomized controlled trial that will examine the feasibility and efficacy of a theory-guided, technology-supported weight loss program. Specifically, a total of 96 obese adults will be randomized to one of three conditions: a) Standard behavioral weight loss program (STND); b) technology-supported behavioral weight loss program (TECH); or c) self-guided behavioral weight loss program (SELF). Differences in weight loss, behavioral adherence, and goal attainment will be examined between groups.

The technology-supported condition will utilize a smartphone application designed to target known health behavior change mechanisms. Participants will be able to track weight and dietary intake, receive real-time feedback on behaviors, and communicate with team members by using a private message board and direct messaging. The application will also connect wirelessly via Blue-tooth to an accelerometer to provide real-time feedback on objectively measured physical activity. The ENGAGED technology will enable participants to experience ongoing support and accountability by allowing study coaches to continuously view participant’s up-to-date data, enabling them to provide timely support in the event of technical difficulties and tailored, immediate feedback during coaching calls.

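### Coaching time is recorded only for calls and their preparation, so the cost-related outcome may understate TECH coach time relative to STND by an unknown amount

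*Protocol article*

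**What the plan says.** Two sections of the protocol article describe the same outcome differently.

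- **Study aims** states the outcome broadly, as a secondary outcome with a cost purpose: "the time spent administering the intervention by lifestyle coaches will also be examined to assess intervention costs".
- **Coaching time**, under Outcome measures, states what is recorded: "Coaches will monitor the number of minutes preparing for and conducting individual coaching calls throughout the first 6 months of the intervention". No other coach activity is listed.

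The arm descriptions show what coaches do.

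- **STND.** Calls are "scheduled on a weekly basis during the initial eight weeks of the study and monthly during months 3–6", and "Coaching calls will last approximately 10–15 minutes". Between calls, "Coaches will review submitted Keeping Track diaries" and grade how far each goal was met.
- **TECH.** Participants also receive regular calls. Coaches see up-to-date participant data, "enabling corrective or supportive feedback to be given via text message or during scheduled coaching calls". Participants are taught to "communicate virtually with their teammates and coach using the ENGAGED application".
- **Discussion.** Continuous access to TECH data is described as "enabling them to provide timely support in the event of technical difficulties and tailored, immediate feedback during coaching calls".
- **SELF.** One 60-minute group session and no coaching calls.

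**The concern.** The outcome named in the aims is the whole of the coaches' time in delivering the programme. The outcome measured is one part of it. A narrower measure would do little harm if the missing part were alike in the arms being compared. Here it is not: the coach contacts outside calls that the article names all belong to TECH. STND's main task between calls, going through paper diaries, fits naturally under call preparation and would be recorded.

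Lower cost is a central motive for the trial, and coach time is the only cost-related measure the article names. Text is offered as an alternative to feedback on a call, so in TECH feedback can move from a recorded channel to an unrecorded one. A lower recorded figure in TECH could then reflect a real saving, a shift of work out of the log, or both. The data as planned could not separate these.

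**Working it through.** The article states no coach-time figure to reproduce. The check compares what is recorded with what is described, then sets a scale.

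**1. Is each named coach activity in the measure?**

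| Coach activity | Where described | Arms | Recorded? |
|---|---|---|---|
| Conducting calls | STND and TECH sections | STND, TECH | Yes |
| Diary review before a call | STND section | STND | Yes, as preparation |
| Viewing the automatic data summary before a call | TECH section | TECH | Yes, as preparation |
| Text-message feedback | TECH section | TECH only | No |
| Messaging through the application | TECH section | TECH only | No |
| Help with technical difficulties | Discussion | TECH only | No |
| Group sessions | STND, TECH and SELF sections | All, in different amounts | No |

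Three of the four unrecorded activities are TECH only. The fourth, group sessions, is eight sessions in both STND and TECH, so it largely cancels in that comparison.

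**2. Scheduled call time.** Eight weekly calls plus four monthly calls (months 3, 4, 5 and 6) make 12. At 10–15 minutes each:

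- 12 x 10 = 120 minutes
- 12 x 15 = 180 minutes

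This is per participant over six months, before preparation. The schedule is stated for STND. Applying it to TECH rests on the TECH section describing a similar programme with regular calls and giving no other schedule.

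**3. Scale of the unrecorded TECH time.** The article gives no minutes for texts, application messages or technical support. As an assumption, take 1 to 5 minutes per participant per week over 26 weeks.

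| Assumed minutes per week | Unrecorded minutes | Share of 180 min | Share of 120 min |
|---|---|---|---|
| 1 | 26 x 1 = 26 | 26/180 = 14% | 26/120 = 22% |
| 5 | 26 x 5 = 130 | 130/180 = 72% | 130/120 = 108% |

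Put the other way, if recorded TECH time is *d* minutes per participant below STND, unrecorded TECH contact of *d*/26 minutes a week removes the difference. A recorded saving of 26 minutes is cancelled by 1 minute a week.

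**4. Comparison with SELF.** Teams have eight members (Randomization).

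- STND and TECH: 8 x 90 = 720 minutes per team, and 720/8 = 90 minutes per participant
- SELF: 60 minutes per team, and 60/8 = 7.5 minutes per participant

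Leaving out group time understates both coached arms against SELF. It can be restored from the schedule without a log.

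**The case against.** The strongest reply is that this is one secondary outcome in a condensed article. No hypothesis in the article says TECH needs less coach time than STND, and the analysis and power sections give coach time no test. The cost argument in the Background is mainly about fewer in-person sessions than the parent programme, a feature STND shares. Text feedback is optional and unscheduled, and may partly replace call content. Technical support appears only in the Discussion, as something the system makes possible, with no volume attached.

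Most of this stands, and it limits the point. It does not remove it: the Coaching time section says what is counted, so the mismatch with the aims is in the text and is not a detail left to a fuller document. The absence of a formal test does not help either, because the aims say the measure will be used to assess costs.

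Three stronger readings are tempting, and the document does not support them.

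- *That the comparison is shown to be biased towards TECH by a large amount.* The direction follows from which arm has the unrecorded channels. The size does not, because no volume of messaging or support is stated. Use could be low, and some coaches might log such contact as preparation, although the definition does not provide for it.
- *That TECH coaches' monitoring of the data display is further unrecorded work.* The TECH section gives coaches up-to-date access and automatic summaries; it prescribes no monitoring between calls. Looking at the summary before a call is preparation, just as diary review is in STND. If automatic summaries shorten preparation, that is a genuine saving.
- *That leaving out group sessions favours TECH over STND.* Both arms have eight sessions. The omission matters only against SELF.

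**Conclusion.** The point holds in a limited form. The aims name coach time in delivering the intervention, for costing; the measure covers only calls and call preparation. The coach contacts left out, apart from group sessions, are described for TECH alone, so the recorded figure may understate TECH coach time relative to STND.

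The amount cannot be found from the article. The 26–130 minutes against 120–180 minutes of scheduled calls rests wholly on the assumed 1–5 minutes a week, and on TECH following the STND call schedule. It shows only that modest unrecorded contact could matter to a cost comparison.

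The weight-loss and adherence outcomes are unaffected. The correction is still worth making before data collection, because these minutes could not be reliably reconstructed afterwards.

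**What to change.** In the Coaching time section:

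1. Have coaches also log, in all arms, minutes spent on text or application messages and on technical support outside calls, in fields separate from call preparation and calls.
2. Define the cost outcome as total coach minutes per participant over the first six months.
3. For any comparison with SELF, add scheduled group-session time divided by team size: 8 x 90 minutes for STND and TECH, 60 minutes for SELF.

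If the log is not changed, label the outcome coaching-call time in both the Study aims and Coaching time sections, and draw no intervention-cost conclusion from it.

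The cost is a few more fields on a log that coaches already have to keep, with a small recording burden. The log should be the source for messaging time. The TECH section describes time-stamped dietary and activity data reaching the server, and does not say that coach messages are captured there.
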